## Abstract

**Background:**

Many older adults with mobility limitations use assistive technology to help them perform daily activities. However, little attention has been paid to the impact on their family caregivers. This neglect produces an incomplete portrayal of the outcomes of assistive technology provision. This paper describes the protocol for a study that examines the impact of a tailored assistive technology intervention that is inclusive of assistance users and their family caregivers.

**Methods/design:**

This research will use a combination of quantitative and qualitative methods. The quantitative portion will be an experimental, single-blinded study in which participants are randomly assigned to either an experimental assistive technology intervention or a standard care group. We will enroll 240 participants (120 dyads) into the study from three Canadian sites. Participants will include older adults (>55) and family caregivers who provide ≥4 h per week of assistance with daily activities and social participation. The primary outcome measure for the older adults will be the Functional Autonomy Measurement System, and the primary outcome measure for the caregivers will be the Caregiver Assistive Technology Outcomes Measure. Qualitative data will be collected through detailed records of the therapists’ interventions, as well as through interviews with dyads and therapists following the interventions. Data collection will occur at baseline (T_0_) with follow-ups at 6 weeks (T_1_), 22 weeks (T_2_), and 58 weeks (T_3_) after baseline evaluation.

**Discussion:**

The findings from this study will help service providers and clinicians to move forward with assistive technology recommendations that are more attuned to the needs of both older adults with mobility limitations and their family caregivers. Additionally, the study’s findings will enhance our conceptual understanding of the spectrum of assistive technology outcomes and set the stage for econometric studies assessing cost-effectiveness.

**Trial registration:**

ClinicalTrials.gov Identifier: NCT01640470. Registered 11/21/2011.

## Background

With the aging population, there is an unprecedented growth of community-dwelling older adults experiencing physical disabilities and limitations of their mobility [1]. Assistive technology (AT) can play an important role in facilitating daily activities and social participation for these individuals [2]. Most commonly adopted AT include mobility-related items such canes, walkers, and wheelchairs, and environmental modifications such as grab bars, raised toilet seats, and bath seats [3, 4]. The use of these devices increases with age, ranging from 14–18 % in a healthy senior population [3] to 45–96 % in frail older adults [5, 6]. Notwithstanding this trend, large numbers of unmet AT needs have been reported in the ageing population [7, 8].

High quality evidence regarding the benefits of AT for older individuals is rare. One example is the randomized control trial (RCT) by Gitlin and colleagues [9]. This study found that the use of AT is associated with long-term positive outcomes with daily tasks, greater self-efficacy, less fear of falling, fewer home hazards, and greater use of adaptive strategies. Despite the potential benefits, adoption of AT by older adults is challenging. Common barriers include limited information about AT use and availability, its cost, and its incompatibility with users’ physical environment [10]. Another concern is the proportion of individuals who discontinue using the devices [11, 12]. To increase the acceptance and adherence to its optimal usage, greater attention to users’ and caregivers’ goals and preferences has been recommended [13, 14].

Insights on AT outcomes for older adults should also include consideration of the caregivers that provide them support. Indeed, a major goal for providing AT to older adults is that it decreases reliance on personal assistance or even replaces it [15–17]. In practice, both AT and human assistance are used by a majority of older people [16, 18–20]. This study is concerned with family caregivers, defined as individuals who provide unpaid assistance to individuals with disabilities [21, 22]. Family caregivers of older adults are frequently either spouses or adult children. In attempting to maintain or enhance the quality of life of those they help, those caregivers may experience a great deal of stress that can lead to their physical or emotional burnout [23]. The potential for burnout poses a challenge to the health care system, as family caregivers provide their unfunded assistance four times more frequently than formal caregivers [24–26]. This value excludes loss of economic productivity associated with time spent providing care, and emotional and physical burden [27].

Two conceptual models contribute to understanding the relationship between AT interventions and outcomes for family caregivers. The first model [28, 29] describes how assistance users’ personal strategies, which frequently include the use of AT, affect them and their family caregivers. Specifically, AT influences the manner and the extent of concerted human help required with activities. In some cases, a very successful outcome with AT may wholly eliminate the need for caregiver assistance, in terms of physical and psychological demands. The second model [30] demonstrates how AT can alter caregivers’ stressors so that their participation, health, and quality of life can be improved. The impact of AT varies with the type of device and the amount and manner in which it is used. The use of AT modulates the relationship among characteristics of primary stressors (e.g., areas of assistance, effort and safety), the features of secondary stressors (e.g., role overload and elective use of time), and broader caregiver outcomes (e.g., health and social participation).

Despite existing theory, little attention has been given to the impact of AT use on family caregivers in experimental studies. Mortenson and colleagues [17] conducted a systematic review suggesting that AT use reduces the degree of physical and emotional effort required when supporting an individual with a disability. However, the studies reviewed were primarily descriptive using cross-sectional data, undermining the strength of the inference. Additionally, the impact of AT use on caregivers was inferred from responses to very few queries, principally dealing with the number of hours of assistance provided. Marasinghe [16] reviewed existing findings to examine whether and how AT reduces caregiver burden. She found that AT contributes to reducing caregiver burden but that AT limitations can also add to their burden. In a previous study, our group [31] conduced a delayed intervention RCT with 44 dyads consisting of community-dwelling older adults and their family caregivers. It was the first experimental study to demonstrate that the provision of AT, embedded in an individually tailored approach, decreases caregiver burden and increases independence for older adults. The design did not, however, provide a parallel comparison group to assess the extent to which the intervention was superior to customary care and, thus, how it actually worked in real life. The findings from this RCT will respond to this gap and also aid in understanding the effectiveness of AT on improving older adults’ functional performance.

### Study goal and hypotheses

This RCT will examine whether a home-based, individually tailored approach to AT provision can improve older adults’ independence and decrease their family caregivers’ perceived burden compared to customary care. We expect that older adults randomized to the experimental condition will have higher activity performance following the novel intervention than those assigned to customary care, and that family caregivers will report significantly reduced burden in their caregiver activities.

*Hypothesis 1*: Compared to AT users in the customary care group, AT users in the experimental group will perform daily activities more independently after completion of the intervention. Secondarily, AT users in the experimental group will also perform instrumental activities of daily living more independently following the intervention.

*Hypothesis 2*: Following the intervention, family caregivers in the experimental group will report a significantly reduced frequency of physical and psychological demands associated with problematic caregiving activities, compared with caregivers in the customary care group. Secondarily, family caregivers in the experimental group will experience a decrease in their overall perceived burden following the intervention.

## Methods/design

The overall study will be based on a randomized controlled experimental design. However, a combination of qualitative and quantitative methods and measures will be used. The advantage of using mixed methods is that they provide multiple perspectives on an intervention’s outcomes so they can be understood more completely [32]. Multiple views also afford the opportunity for data triangulation, thus increasing the credibility of the findings. Throughout the course of administering the intervention, the therapists carrying out the experimental approach will record their impressions about both the successful and unsuccessful aspects of the intervention. A purposeful sample of dyads from both groups will be interviewed about their experiences after completing the intervention and at the conclusion of the study. Any changes to the protocol will be made through the trial registry. The anticipated end date of the study will be March 31, 2017.

### Quantitative study design

This study protocol follows CONSORT guidelines. A single blind RCT will be conducted with 120 dyads, each consisting of an older AT user and his or her principal family caregiver. Both the experimental and customary care interventions will be provided to participants after the administration of the outcome measures at baseline. The measures will be re-administered to both groups 6 weeks, 22 weeks (the main trial endpoint), and 58 weeks after baseline evaluation. Figure 1 depicts the study design.

**Fig. 1 Fig1:**
[figure not shown]
ATPUT, Assistive Technology Provision, Updating and Tune-Up intervention

### Participants

Participants will be recruited from three sites in Canada: Montreal, Ottawa and Vancouver. To be eligible for the study, a dyad must consist of one assistance user and a one family caregiver. Assistance users must be (a) age 55 years or older, (b) living at home, (c) have a mobility limitation qualifying them for referral for homecare services, and (d) needing assistance with daily activities or social participation for a total of 4 h or more per week. Users may include individuals who currently are not using AT or are experiencing problems with their current devices. The population of interest is based off the amount of assistance received rather than on the diagnosis, because the use of AT is not diagnosis specific and there can be great heterogeneity among individuals with specific diagnoses. The family caregiver must be (a) age 18 years or older, and (b) delivering unpaid assistance with daily activities or social participation for a total of 4 h or more per week for at least 1 month. It is not required that assistance users and family caregivers reside together.

Dyads will be excluded if either member has a degree of cognitive impairment likely to prevent her or him from reliably completing the study questionnaires or if either has an advanced terminal illness. Cognitive status will be measured with the Montreal Cognitive Assessment (MoCA), a cognitive screening test designed to be sensitive to mild deficits. It has good test-retest reliability (correlation coefficient = .92) and internal consistency (Cronbach *α* = .83) [33].

### Recruitment

Participating dyads will be either existing clients or clients who have been recently referred to home care for occupational therapy services at the Montreal, Ottawa and Vancouver sites. Montreal participants will be recruited through the West Island Health and Social Services Center, Ottawa participants through the Community Care Access Centers, and Vancouver participants through the Vancouver Costal Health network. Candidates will be identified and recruited via referral lists and initially screened by home-care staff to ensure eligibility criteria are met. The sites’ study coordinators will then contact all interested individuals to confirm their eligibility, fully explain the project, answer questions, and obtain consent. Study participants will be permitted to withdraw from the intervention at any time they desire or if they become too ill. Due to ethical constraints the investigators cannot compel those who withdraw to provide further data. If the participant voluntarily discloses the reason for withdrawal, these will be documented.

### Randomization and blinding

Study coordinators at each site will randomly assign participants into the experimental group or control group immediately following their recruitment. The experimental group will consist of dyads that receive the home-based AT Provision, Updating and Tune-Up (ATPUT) intervention. Control group dyads will receive the customary care prevailing at the site where they were recruited. Centralized randomization software will be used to obtain the same number of participants in each group (www.randomization.com). Participating dyads will be blinded regarding their group assignment to the extent that they will be unfamiliar with the intervention received by the other group. Raters administering the outcome measures will be blinded until completion of the trial. Owing to the nature of the intervention, however, it is unfeasible to blind the study coordinators or the occupational therapists providing the intervention.

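### As written, dyads are allocated before the baseline visit that holds the outcome measures and the MoCA, so a cognitive exclusion could arise after randomisation and conflict with the intention-to-treat rule

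*Protocol article*

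**What the plan says.** All references are to the protocol article.

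- **Randomization and blinding:** site coordinators will "randomly assign participants into the experimental group or control group immediately following their recruitment". They use centralized software that yields equal group sizes. Raters stay blinded throughout; coordinators and treating therapists do not. Dyads are blinded only in that they do not know what the other group receives.
- **Recruitment:** home-care staff carry out a first eligibility screen of candidates taken from referral lists. After that step, "study coordinators will then contact all interested individuals to confirm their eligibility, fully explain the project, answer questions, and obtain consent". No testing is mentioned in this section.
- **Quantitative study design:** both interventions "will be provided to participants after the administration of the outcome measures at baseline". This ties baseline to the start of the interventions and says nothing of its place relative to randomisation.
- **Participants:** "Dyads will be excluded if either member has a degree of cognitive impairment likely to prevent her or him from reliably completing the study questionnaires". The section then names the MoCA as the measure of cognitive status and gives no cut-off.
- **Quantitative measurements, with Table 2:** raters give all quantitative measures. SMAF, CATOM and MoCA all appear in the baseline column. The MoCA is listed among the clinical data for AT users only. A footnote says it is repeated later only if raters notice major changes.
- **Quantitative data analysis of primary and secondary outcome measures:** the analysis is by intention to treat, with every participant kept in the allocated group. Multiple imputation is to be explored for missing data.

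**The concern.** Eligibility tests and baseline values should be fixed before anyone knows the arm. Three things are at stake if they are not.

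1. An exclusion criterion may come to light after allocation, and the plan then gives two incompatible instructions for that dyad.
2. Baseline scores may no longer be independent of allocation. This matters most for the CATOM, the primary caregiver outcome, because it is the caregiver's own report of burden.
3. Dyads may leave between allocation and T0, possibly at different rates by arm, and would have no outcome data at all. The Recruitment section accepts that those who withdraw cannot be made to give further data.

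**Working it through.** The point concerns order and roles. The plan states no figure to reproduce, so the check sets the sections side by side.

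**Step 1. When does allocation happen?** Randomization and blinding puts it directly after recruitment. Recruitment consists of home-care screening, confirmation of eligibility by the coordinator, explanation and consent. Allocation therefore follows consent.

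**Step 2. When does T0 happen?** Quantitative study design says only that it precedes the interventions. Raters conduct it, and they have no part in the steps described under Recruitment. T0 is thus a separate step, with a different person, from the one that allocation immediately follows.

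**Step 3. Where does the MoCA fall?** Table 2 puts it at baseline, and raters give the measures in that table. The footnote on repeating it when raters see major changes fits a first administration by raters at T0. The Recruitment section does not mention it.

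**Step 4. Resulting order.** Consent, allocation, T0 with the MoCA, intervention. No section states the reverse order.

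**Step 5. Apply the rules to a dyad whose impairment is found at T0.**

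- Participants: the dyad is to be excluded.
- Data analysis: the dyad has been allocated and is to be kept in its group.

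Both cannot be followed. If the dyad is excluded, the exclusion rests on a judgement (no cut-off is given) made when the unblinded coordinator already knows the arm. If it is kept, the analysis contains questionnaires that the criterion was written to keep out.

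**Step 6. Apply the order to baseline scores and early withdrawal.** Blinded raters protect the scoring. They do not protect what a caregiver reports about burden if the caregiver already has some idea of the service to come. Dyad blinding is partial, and the text does not say what dyads are told between allocation and T0. A dyad that leaves in that interval has no measurement at any time point. It can enter the planned repeated measures analysis of variance only through imputation, which the plan undertakes only to explore.

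**Step 7. Test the other reading.** Suppose the MoCA is done when eligibility is confirmed and merely tabulated under baseline. The conflict in step 5 then largely disappears. The SMAF and CATOM would still follow allocation, because nothing places them inside recruitment. So step 6 stands under either reading of the MoCA.

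**The case against.** The strongest reply is that the order is inferred. No sentence says that randomisation precedes T0, Figure 1 is not available, and eligibility is said to be confirmed before consent. This stands as a limit on certainty. It does not supply the opposite order, and the one explicit statement of timing places allocation directly after recruitment.

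Second, the cognitive criterion is a judgement about completing questionnaires. It covers both dyad members, whereas Table 2 lists the MoCA for AT users only. This also stands: the MoCA is the named measure of cognitive status, and a reader who infers that a MoCA score decides exclusion goes beyond the text. The mismatch is itself something to reconcile.

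Third, the plan has real safeguards. Raters are blinded, so the coordinator's knowledge of the arm is not shown to reach the scoring of T0. Central software makes the assignment. Intention to treat keeps everyone as allocated, and imputation is contemplated, so it would be wrong to say that a dyad without T0 can never be analysed. These narrow the risk, but they do not settle which rule applies to a dyad found ineligible after allocation.

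A reader might also infer selection bias, since the unblinded coordinators who confirm eligibility also assign, and group sizes are forced equal. That requires the next assignment to be foreseeable. The article does not describe blocking or concealment, and a condensed article may leave both to the full protocol. The same silence covers stratification by site. None of this shows a predictable list or an unstratified one, and a site term in the primary model does not follow from the order of events.

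**Conclusion.** The point holds as a sequencing fault that should be corrected. Followed as written, the protocol allocates before T0. That leaves a contradiction between the exclusion rule and the intention-to-treat rule, and exposes self-reported baseline CATOM and pre-T0 withdrawal to knowledge of allocation. The conclusion rests on two assumptions: that recruitment means what the Recruitment section describes, and that the MoCA is given with the other Table 2 measures at T0.

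Exclusion after randomisation is a risk created by the order; the documents do not plan it as a procedure.

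The size cannot be stated, because no rate is given for impairment found at T0 or for withdrawal before T0. A reader might be tempted to add such losses to the dropout allowance and report lost power. The documents do not support that: any rate would be invented, and some of the loss may already lie within the 20% allowance. The plan's own figures leave 120 × 0.80 = 96 dyads against the 102 required whatever the order of randomisation, so that shortfall is a separate matter.

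**What to change.** Change the first sentence of Randomization and blinding so that the central software releases an assignment only when three conditions are met:

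1. the dyad is registered;
2. eligibility is confirmed, including any cognitive test used for exclusion;
3. all T0 measures are completed and entered.

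Then reconcile the other sections:

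- **Quantitative study design:** place baseline before randomisation as well as before the interventions.
- **Participants and Recruitment:** say at which step cognitive status is assessed for exclusion.
- **Table 2:** show whether the MoCA serves eligibility or description only, and for which dyad members.

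The cost is a short delay between consent and allocation. It reorders one step and needs no extra visit. Follow-up is timed from the baseline evaluation, so the assignment should be released promptly once T0 is entered. If sites already work in this order, the change is only to the wording.

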### Customary intervention

Current AT interventions in Canada take place in the community and are provided by registered occupational therapists. According to collaborators at the participating sites, customary interventions are not standardized. For example, family caregivers are not required to be included within the intervention process. Individuals are provided with equipment based on local funding policies and have limited practice time with devices. Follow-up visits are at the discretion of the therapists. Participants in the control group will receive services provided to clients by the health authorities within the study, with no additional intervention from the study.

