### Quantitative sample size

Sample size was calculated for the primary endpoint (22 weeks) for older adults and family caregivers separately and the largest sample size was selected. The sample size for the primary caregiver outcome measure (CATOM) was chosen to detect a 10 % decrease in perceived burden. This is consistent with the caregiver burden change noted in a prior trial using CATOM scores at baseline and after 16 weeks [31]. It indicates a one-level decrease on half of the items for the family caregivers (nearly always → frequently → sometimes → rarely → not at all). The primary older adults’ outcome measure is the SMAF. The sample size was chosen in order to detect an improvement of 9 % following the intervention. This value is intermediate between the minimal detectable difference and the change measured by administering the SMAF in a study examining the impact of a rehabilitation program on individuals with post-cerebral vascular accident [44, 45].

To determine an effect size, Cohen’s *D* was calculated using standard deviations from our prior study [31] and then transformed into Cohen’s *F* [46, 47]. As the effect size was smaller for the SMAF, we used this value to simulate various potential scenarios using G*Power 3.1.0.87. For these simulations we varied several variables including 1) effect size (0.13 to 0.15), 2) correlations among repeated measures (which previous data suggest will be moderate for pre-post intervention and strong between post intervention and long term follow up, e.g. 0.5 to 0.6), and 3) violations of sphericity (due to differences in variances over time, e.g., 0.6 to 0.9). The average of these sample sizes is 102. Based on approximately a 20 % dropout rate for the main trial endpoint (suggested by the prior study in which dropout occurred exclusively due to health related issues, which are common in this population), a sample of 120 dyads will be recruited (40 from each site).

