### Quantitative data analysis of primary and secondary outcome measures

Data will be entered by raters into SPSS statistics data editor (IBM SPSS Statistics) immediately after each evaluation session to decrease the likelihood of missing data. The use of multiple imputation will be explored to deal with any missing data, especially if a participant is unable to be assessed at one of the data collection time-points [48].

To ensure baseline similarity between groups, the experimental and control groups will be compared on socio-demographic and clinical variables with the use of *t*-tests for continuous data and Chi-square for nominal data. Descriptive statistics and histograms will be used to display differences between the groups. A repeated measures analysis of variance will be conducted to analyze dependent variable data, using a Greenhouse-Geisser correction to address issues with sphericity.

Scores for the primary outcome measures (SMAF and CATOM, items 1–14) will be compared between treatment groups over time using an intention-to-treat analysis. Intention-to-treat analysis dictates that all participants are included in the group to which they were allocated for purposes of analysis, whether or not they completed the intervention for that group. The same analysis will be applied to secondary outcome measures, which include the RNLI, CATOM (items 15–18), CBI, self-report FIM and hours of care provided by family caregivers. These secondary outcome analyses will be considered exploratory in view of the increased likelihood of Type I errors resulting from multiple statistical comparisons. Sensitivity analyses will be performed to compare the effect of the interventions on 1) caregiving spouses versus caregiving adult children, and 2) on participants receiving services at the different sites.

To test for changes in family caregiver burden due to the intervention, changes in older adults’ SMAF scores will be correlated with changes in their caregivers’ CATOM scores, using either a Pearson or Spearman correlation depending on the distribution of the data.

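### The stated primary ANOVA for SMAF and CATOM has no site term although control care is defined by site; prespecifying one is nearly free, for a modest gain in precision

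*Protocol article*

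**What the plan says.** - **Allocation** (Randomization and blinding): "Study coordinators at each site will randomly assign participants into the experimental group or control group immediately following their recruitment". The only balance promised is equal group totals: "Centralized randomization software will be used to obtain the same number of participants in each group". Whether there is one list or one per site is not said.
- **Control treatment** (Randomization and blinding): "Control group dyads will receive the customary care prevailing at the site where they were recruited".
- **What that care is** (Customary intervention): "customary interventions are not standardized", and "Individuals are provided with equipment based on local funding policies". Practice time with devices is limited, and follow-up visits are left to the therapist.
- **Site sizes** (Quantitative sample size): "a sample of 120 dyads will be recruited (40 from each site").
- **Primary analysis** (Quantitative data analysis of primary and secondary outcome measures): "A repeated measures analysis of variance will be conducted to analyze dependent variable data, using a Greenhouse-Geisser correction". SMAF and CATOM items 1–14 are compared between groups over time by intention to treat, and the secondary outcomes in the same way. No site factor or other covariate is named. Site enters only afterwards, when the effect of the interventions is compared across sites as a sensitivity analysis.
- **Discussion**: many participant and environment factors are expected to influence the results, and enough power to control for them is called important. The stated model controls for none.

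**The concern.** Equipment funding, practice time and follow-up visits plausibly affect how much a dyad changes, and the article says that customary care is neither standardised nor independent of local policy. Site is therefore a likely source of variation in the outcome that both primary tests address. The sensitivity comparison asks whether the effect differs between sites; it does not remove site variation from the primary estimate or its standard error.

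At stake is precision, not validity. The planned effect is small (Cohen's f 0.13 to 0.15), and the sample has little to spare: 120 × 0.80 = 96 dyads would remain after the stated dropout, against the stated 102.

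**Working it through.** **The plan's own figure.** The average sample size of 102 cannot be reproduced from the article alone, because alpha, power and the number of measurements are not given. For the group-by-time test at alpha 0.05, averaging over f 0.13–0.15, correlation 0.5–0.6 and sphericity 0.6–0.9 gives 104.8 with four measurements and 90% power, 94.7 with three and 80%, and 80.7 with four and 80%. Nothing below depends on which was used.

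**Which site differences matter.** In a group-by-time test each dyad is compared with itself, so a stable difference in level between sites cancels. Only differences between sites in *change* count. They are removed by the site-by-time term; a site main effect alone would not do it.

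**Model for the check.** One change score per dyad with total variance 1; 120 dyads, 40 per site, 60 per arm. Site explains an assumed share s of the variance, with site means of −√(1.5s), 0 and +√(1.5s). The effect is 0.515 SD, chosen to give 80% power without a site term; it is not the planned effect. There were 6,000 simulated trials per setting.

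**Standard error by formula.**
- Without site: √(4/120) = 0.183.
- With site and balanced sites: √(4(1−s)/120), which is 0.178 at s = 0.05 and 0.173 at s = 0.10, or 2.5% and 5.1% smaller.
- With unstratified allocation the simulated gain is a little less: 0.182 to 0.179 at 5% (about 2%) and 0.184 to 0.176 at 10% (about 4%).

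**Power and type I error, simulated.**

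| Assumed site share of change variance | Unstratified: power without → with site | Stratified: power without → with site | Stratified, site omitted: type I error |
|---|---|---|---|
| 0 | 80.3% → 79.5% | 80.1% → 80.0% | 0.054 |
| 0.02 | 80.4% → 80.6% | 80.2% → 80.6% | 0.044 |
| 0.05 | 80.1% → 81.3% | 81.3% → 82.6% | 0.038 |
| 0.10 | 79.7% → 82.7% | 81.0% → 83.7% | 0.041 |
| 0.20 | 79.9% → 86.9% | 82.9% → 88.0% | 0.030 |

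The simulation error of a rate near 0.05 is √(0.05 × 0.95/6000) = 0.003. As a cross-check on the last column, the large-sample rate is 2[1 − Φ(1.96/√(1−s))]: 0.048, 0.044, 0.039 and 0.028 at shares of 0.02, 0.05, 0.10 and 0.20. That agrees within simulation error, allowing for some scatter at 0.05.

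With unstratified allocation and no site term, the simulated type I error was 0.050–0.052 at every share. The unadjusted test is then valid, and the cost is precision only.

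**The case against.** **Omission rather than error.** An unadjusted comparison of randomised groups is valid, and a full list of model terms often belongs in the analysis plan. This is fair as far as it goes. But the article does state its primary model and does place site, in a sensitivity comparison only. Recommending a site term therefore improves on what is stated and is more than a request for detail.

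**The allocation reading.** A reader might infer that allocation is balanced only overall. On that reading the number in one arm at a site of 40 has SD 2.6 (hypergeometric, 60 of 120), and at least one site would split 24:16 or worse with probability about 0.36. The documents do not support the inference: coordinators at each site assign, 40 dyads per site are planned, and separate site lists fit the text equally well.

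**Bias.** A reader might also call chance site imbalance confounding. With one site at 24:16 and another at 16:24, the estimate shifts by 8/60 = 0.13 of the difference between those sites in mean change, or 0.067 SD for an assumed 0.5 SD difference. That shift is random over allocations and already contained in the standard error of 0.183 SD. It is not an additional or systematic error.

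**Mismatch of remedy and reason.** Site-specific control care points mainly to a treatment effect that varies by site, which site and site-by-time terms do not describe. This stands. The planned comparison across sites addresses it and should stay, as exploratory; the site terms serve precision only.

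**Conclusion.** The point holds as a recommendation about the primary model. Site belongs in it because control care is site-specific by design and the term costs almost nothing. Whether allocation is stratified need not be known: if it is, the omission makes the test conservative; if it is not, site differences in change inflate the error. Neither case produces excess false positives.

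The size is modest and rests wholly on the assumed site share of the variance in change, for which the article gives no figure. From 80% power the gain with unstratified allocation is about 1 point at 5%, 3 at 10% and 7 at 20%, and next to nothing at 2%. If sites do not differ in change at all, the term loses up to about 1 point. The simulations use all 120 dyads and a single change score, so they indicate scale and do not predict the power of the planned test.

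**What to change.** In the section on analysis of primary and secondary outcomes, prespecify site (three levels) as a fixed between-subject factor, with its site-by-time term, in the SMAF and CATOM models and in the secondary models. Leave treatment-by-site terms out of the primary model and label the planned comparison across sites as exploratory.

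The cost is 2 between-subject degrees of freedom and, with four time points, 2 × 3 = 6 for site-by-time. Before any sphericity correction or dropout, the within-subject error falls from 118 × 3 = 354 to 116 × 3 = 348. No new data are needed, since each dyad's site is known. If allocation is stratified by site, one sentence saying so would also explain the term.
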